# Integrative medicine rehabilitation for children with cerebral palsy: a study protocol for a multicenter pragmatic randomized controlled trial

**DOI:** 10.1186/s13063-020-04639-x

**Published:** 2020-08-17

**Keywords:** Cerebral palsy, Rehabilitation, Gross motor function measure (GMFM), Integrative medicine rehabilitation (IMR), Goal attainment scale (GAS), Korean Bayley scales of infant development III (K-BSID III), Pediatric quality of life inventory (PedsQL), Children, Randomized controlled trial

## Abstract

**Background:**

Traditional Korean medicine (TKM) has been employed for the treatment of children with cerebral palsy in Korea; however, the addition of TKM to usual rehabilitation (UR) treatment is hindered by insufficient evidence of clinical improvement with TKM in patients with cerebral palsy. In this study, we will evaluate the effectiveness and safety of integrative medicine rehabilitation (IMR) for cerebral palsy through a randomized controlled clinical study.

**Methods:**

Eighty children (2–6 years old) diagnosed with cerebral palsy will be recruited and randomly divided into groups A and B. Patients in group A will receive IMR with UR, while those in group B will receive only UR during weeks 1–12 of the study. IMR includes acupuncture treatment (head and limb acupuncture) three times a week and the administration of herbal medicine (Yukgunza-tang and Yukmijihwang-tang extracts) twice a day in parallel with UR. Evaluations will be conducted at the beginning of the study and at 12 and 24 weeks (follow-up). The primary outcome is the Gross Motor Function Measure-88 score, and the secondary outcomes are the scores for the Goal Attainment Scale, Korean Bayley Scales of Infant Development III, and the Pediatric Quality of Life Inventory, and adverse events.

**Discussion:**

This will be the first pragmatic randomized controlled trial to evaluate the efficacy and safety of IMR in children with cerebral palsy in Korea. The results will help to demonstrate if IMR is an effective therapeutic approach for cerebral palsy.

**Trial registration:**

Ministry of Food and Drug Safety 31361 (http://www.mfds.go.kr). Registered on 29 June 2017. Clinical Research Information Service KCT0002620 (https://cris.nih.go.kr/cris/search/search_result_st01.jsp?seq=9819). Registered on 29 December 2017.

## Background

The worldwide prevalence of cerebral palsy (CP) is estimated to be 2–2.5 cases per approximately 1000 survivors, with a prevalence rate of 0.26% among children in Korea. Korea has the lowest fertility rate among the Organization for Economic Cooperation and Development countries. However, with the increase in the number of multiple births owing to the increase in in vitro fertilization and the subsequent increase in the proportion of preterm infants, the prevalence of CP is increasing [1].

Children with CP show various restrictions on physical activity due to impaired motor functions and posture. Thus, CP treatment involves multiple approaches including usual rehabilitation (UR; physiotherapy, occupational therapy, speech therapy, and orthopedic rehabilitation therapy), injection therapy, medication, and surgical treatment [2]. Traditional Korean medicine (TKM) has also been employed for the rehabilitation of children with CP [3–5]. Integrative medicine rehabilitation (IMR) is the addition of acupuncture and herbal medicine treatment to UR for CP. Numerous clinical studies in China have reported the remarkable efficacy as well as the adverse effects of acupuncture treatment, chuna therapy, and herbal medicine treatment in children with CP [6]. However, the effectiveness of IMR in patients with CP is still controversial in Korea as the Korean and Chinese traditional medicine theories and clinical applications are different which restrict extrapolation. More definitive clinical studies are needed for the medical insurance coverage of TKM treatment for CP.

### Objectives

To address this lacuna in the literature, this study aims to administer acupuncture and herbal medicine treatment simultaneously with UR therapy for 12 weeks and compare the findings with those obtained using UR alone. The Gross Motor Function Measure-88 (GMFM-88), Goal Attainment Scale (GAS), Korean Bayley Scales of Infant Development III (K-BSID-III), and Pediatric Quality of Life Inventory (PedsQL) scores have been selected as outcome variables. A rigorously designed large-scale multicenter pragmatic randomized trial will clarify whether IMR can facilitate clinical improvement in children with CP.

### Trial design

Multicenter, pragmatic, randomized-controlled, evaluator-blinded trial.

## Methods/design

### Patients

#### Inclusion criteria

Participants must meet the following conditions to be eligible: (1) aged 2–6 years and diagnosed with CP according to a combination of clinical findings and cerebral magnetic resonance imaging and (2) parental consent for participation in the study.

#### Exclusion criteria

Participants meeting any of the following criteria will be excluded: (1) orthopedic surgery in the preceding 6 months; (2) Botox treatment in the preceding 6 months; (3) a history of degenerative brain disease, congenital neuromuscular disease, or uncontrolled seizures; (4) participation in other clinical trials in the preceding 3 months; (5) a history of serious diseases (such as tumors, heart disease, or severe infectious diseases) other than CP; (6) difficulty accepting acupuncture and/or herbal medicine treatment; (7) abnormalities in the degradation and absorption of lactose or galactose; (8) a history of liver- or kidney-related diseases; and (9) sensitivity to medicines.

### Patient and public involvement

Although not directly involving patients, the number and duration of acupuncture treatments and patient position for acupuncture administration were determined for the study design to ensure patient comfort in consultation with a skilled TKM doctor and physical therapist experienced with treating CP patients.

The individual goals for GAS (secondary outcome measure) will be set by the patients, guardians, and the researcher; however, they will be assessed by the researchers only. The guardians submitting the written consent will also complete the PedsQL™ questionnaire for the quality of life evaluation of children with CP. The results will be disseminated by publication in a peer-reviewed journal, presentation at international congresses, and via telephonic communication to the patients.

### Study design

This is a multicenter pragmatic randomized controlled evaluator-blinded clinical trial of the effectiveness of IMR for CP. We will recruit participants by advertising on the Internet and through posters in hospitals and communities. The recruiting period will be from January 1, 2021, to December 31, 2022.

After explaining the “Guide for Study Subjects” to the participants’ guardian, their consent for clinical study participation will be obtained by the study investigators. The Guide for Study Subjects contains information on the effects of the study and adverse reactions as well as the safety data. The evaluations will be carried out after receipt of the consent forms. On the consent form, participants will be asked if they agree to the use of their data should they choose to withdraw from the trial. Participants will also be asked for permission for the research team to share relevant data with people from the Universities and hospitals taking part in the research. This trial does not involve collecting biological specimens for storage.

The participants will be randomly stratified into groups A and B. Randomization will be performed based on the Gross Motor Function Classification System (GMFCS) stage (stages 1–3 vs. stages 4–5), age (1–2 years vs. 4–6 years), and CP type (spastic vs. non-spastic). The principal researcher will use a block randomization method using a random block size to generate the random allocation sequence. Computer-assisted randomization will be performed using the Excel 2010 program, and the randomized sequences will be delivered in an opaque envelope to conceal allocation. After screening, the researcher will open the sealed envelope in the presence of the participant, and the assignment result will be confirmed.

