#### Herbal medicine

The herbal medicine used in this study is a combination of Yukgunza-tang and Yukmijihwang-tang extracts prepared by Kracie Pharma Korea Co. which is licensed by the Korea Food and Drug Administration and produced by a GMP-approved facility. The Yukgunza-tang extract contains the following raw materials (in an adult dose per day basis, 6 g): Ginseng Radix 4.0 g, Atractylodes Rhizoma Alba 4.0 g, Smilacis Rhizoma 4.0 g, Pinelliae Tuber 4.0 g, Fraxini Cortex 2.0 g, Zizyphi Fructus 2.0 g, Glycyrrhizae Radix 1.0 g, and Zingiberis Rhizoma 0.5 g. The Yukmijihwang-tang extract contains the following raw materials (on an adult dose per day basis, 6 g): Rehmanniae Radix 5.0 g, Cornus Fructus 3.0 g, Dioscoreae Rhizoma 3.0 g, Alismatis Rhizoma 3.0 g, Smilacis Rhizoma 3.0 g, and Moutan Cortex 3.0 g. Yukmijihwang-tang helps improve cognitive functions, self-organization, and social development [5, 12–15], and Yukgunza-tang improves gastrointestinal functions which facilitate food intake and promote growth in children [16, 17].

The medication doses are as follows: (1) for patients aged 12–47 months, a total dose of 4 g per day (Yukgunza-tang, e.g., 2 g, + Yukmijihwang-tang, e.g., 2 g), and (2) for patients aged 48–72 months, a total dose of 6 g per day (Yukgunza-tang, e.g., 3 g, + Yukmijihwang-tang, e.g., 3 g). The pediatric dose has been determined in accordance with the TKM pediatric science textbook. Patients will consume the herbal medicine with drinking water twice a day about 1 h after breakfast and lunch.

The researcher will check if the participant is taking the herbal medicine twice a day and will provide 2–3 days of herbal medicine at each visit. If the patient is unable to consume the herbal medicine, the duration of and reason for the discontinuation will be recorded on a separate chart. The researcher will check whether the stock and usage records of the herbal medicine match.

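### The randomisation age strata (1–2 and 4–6 years) do not cover the eligible range of 2–6 years: 3-year-olds have no stratum

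*Protocol article*

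**What the plan says.** The Inclusion criteria admit children "aged 2–6 years and diagnosed with CP according to a combination of clinical findings and cerebral magnetic resonance imaging". The Abstract gives the same range: "Eighty children (2–6 years old) diagnosed with cerebral palsy will be recruited".

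The Study design section names three stratification factors. The first is "Gross Motor Function Classification System (GMFCS) stage (stages 1–3 vs. stages 4–5", the second is "age (1–2 years vs. 4–6 years", and the third is CP type, spastic or non-spastic. Sequences are to be generated by block randomisation with random block size and delivered in opaque envelopes. A researcher opens the envelope after screening, with the participant present. The same section lists four recruiting hospitals.

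The Herbal medicine section uses two age bands. The lower is worded "for patients aged 12–47 months" and the upper runs from 48 to 72 months. The Statistical analysis section includes age as a fixed-effect covariate.

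**The concern.** Stratified randomisation needs every eligible child to fall into exactly one stratum, fixed by baseline data. The GMFCS and CP-type factors meet this, since each pair of categories takes in all children. The age factor does not: it jumps from 2 years to 4 years and starts a year below the eligibility limit.

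At stake is the allocation rule itself. When a 3-year-old passes screening, the article gives no stratum to allocate from. Staff can choose one of the two age strata on the spot or refuse a child who meets the criteria. The first option weakens the balance on age that the stratification is meant to provide, and the four sites may not choose alike. The second removes an eligible age group without any criterion saying so.

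**Working it through.** The article gives no figure of its own for this point, so the check compares the stated age ranges.

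**Inputs**
- Eligible ages: 2–6 years (Inclusion criteria, Abstract).
- Stratum ages: 1–2 and 4–6 years (Study design).
- Age bands used elsewhere: 12–47 and 48–72 months (Herbal medicine).
- Planned sample: 80 children, 40 per group (Study design).

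**Step 1: completed years**
- Eligible ages: {2, 3, 4, 5, 6}. Ages in some stratum: {1, 2} ∪ {4, 5, 6} = {1, 2, 4, 5, 6}.
- Eligible but in no stratum: {3}.
- In a stratum but not eligible: {1}.

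**Step 2: months**
- The lower stratum covers 12–35 months and the upper starts at 48 months. The uncovered span is 36–47 months, which is 12 months wide.
- Of the lower stratum's 24 months, 12 (12–23 months) lie below the eligibility limit. Only 2-year-olds can fill it.

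**Step 3: are 3-year-olds meant to be in the trial?**
- No exclusion criterion mentions them.
- The Herbal medicine bands run without a break from 12 to 72 months, so 36–47 months falls inside the lower band.
- The K-BSID III section uses that scale for children under 42 months, which takes in ages 36–41 months.

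The gap is therefore not a deliberate restriction that another section explains.

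**Step 4: size of the gap**

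The article gives no age distribution. Assume that ages are uniform over the eligible range, and take both readings of its upper end:

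| Upper end of eligibility | Share in the gap | Of 80 children |
|---|---|---|
| Through age 6 (24–83 months) | 12/60 = 20% | 16 |
| Ends at 72 months, counted as completed months 24–72 | 12/49 = 24.5% | about 20 |
| Ends at 72 months, as a span of 48 months | 12/48 = 25% | 20 |

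**Step 5: sample size**

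A difference of 2.8 with SD 3.2, two-sided 5% and 90% power gives 28 per group by the normal approximation, and 28/(1 − 0.30) = 40. This reproduces the article's figures, and none of them depends on the strata.

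**The case against.** The strongest reply is that this is a one-digit slip. The upper stratum begins at 4 years, exactly where the Herbal medicine bands divide, so the lower stratum was probably meant to end at 3. That is plausible. But the article does not say so, and a lower stratum of 1–3 years would still name an age that cannot enrol. The slip also sits in the sentence that defines the allocation, so it has to be corrected whatever its origin.

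A reader might infer several stronger points that the documents do not support:

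- **Concealment fails.** Choosing between sets of sealed, opaque envelopes does not reveal the next assignment, and random block sizes limit prediction. That envelopes are held by stratum is itself an inference from the stratified block design. What stands is an ad hoc choice of stratum.
- **Imbalance would distort the result because age strongly predicts motor gain.** The article does not say this. It also adjusts for age in the model, which reduces the effect of a chance imbalance.
- **The strata conflict with the dosing bands as a separate fault.** The 4-year bound already coincides with the 48-month division. What differs is the end of the lower stratum, which is the same gap seen again.
- **The 1-year-olds would be misallocated.** Eligibility keeps them out, so that part of the stratum simply stays empty.

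It is also fair to say that a site could ask for clarification at its first 3-year-old, so the 16–20 children are not certain to be lost or misplaced.

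**Conclusion.** The point holds as a contradiction within the protocol article. The age strata are not exhaustive over the eligible range: children aged 36–47 months have no stratum, and age 1 is listed although it is ineligible. This rests on the text alone.

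Its size rests on an assumption. With uniform ages it concerns about 20–25% of the sample, or 16–20 of 80 children; another age mix would change the count but not the gap. The supported consequence is weaker age stratification, with handling that may differ between the four sites, or the refusal of eligible children. The documents do not show that the primary comparison, the type I error or the sample size is compromised. The correction is still needed before the lists are generated, because the allocation rule cannot be followed as written for an eligible age group.

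**What to change.** Restate the age factor in the Study design section so that the strata are exhaustive and lie within eligibility. One example is 2–3 years (24–47 months) versus 4–6 years (48 months or older), with age taken at randomisation. Generate the allocation lists and envelopes from that definition and give all four hospitals the same wording.

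The analysis model need not change. The age covariate in the Statistical analysis section can stay, and forcing the two age bands into the model would be a preference rather than a correction.

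The cost is one line of protocol text and lists built to match. The article was published in August 2020 and gives January 2021 as the start of recruitment, so on its own dates the change can precede the first randomisation.

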**Fig. 1 Fig1:**
[figure not shown]
Flow chart of the study design. First, we will recruit 80 participants from multiple centers. Participants will be randomly assigned to groups A (*n* = 40) and B (*n* = 40) after baseline assessment. Second, all participants will continue UR (physiotherapy, occupational therapy, etc.), as they had been doing previously, throughout the 24-week study period. Third, over weeks 1–12, group A will receive additional IMR comprising acupuncture and herbal medication with UR, and group B is a waiting group that will receive only UR. Participants will be assessed at 12 weeks. Fourth, group B will receive 12 weeks of acupuncture and herbal medication with UR during weeks 13–24; group A will continue UR during weeks 13–24 and return to the institution for follow-up assessment at 24 weeks. The researchers will then collect the results and analyze the data. Abbreviations: UR, usual rehabilitation; IMR, integrative medicine rehabilitation

**Fig. 2 Fig2:**
[figure not shown]
Standard Protocol Items: Recommendation for Interventional Trials (SPIRIT) schedule of enrollment, interventions, and assessments. GMFCS, Gross Motor Function Classification System; GMFM, Gross Motor Function Measure; K-BSID III, Korean Bayley Scales of Infant Development III; GAS, Goal Attainment Scale; PedsQL, Pediatric Quality of Life Inventory

The assessments will be performed three times in total: at baseline, 12 weeks (after 3 months), and 24 weeks (after 6 months). Two physical therapists with more than 5 years of experience in pediatric rehabilitation will evaluate the scores for each item and the recorded videos (the videos will be recorded by a physical therapist during assessment to evaluate the participants’ GMFM-88, GAS, and K-BSID III developmental status). In principle, the same person should conduct all three evaluations. Assessors will be blinded to the subject assignment, and an inter-rater reliability test will be conducted before each study. The proposed study protocol is schematically presented in Figs. 1 and 2.

Sample size calculations are based on a previous study [8]. We estimated a GMFM-88 score difference of 2.8 ± 3.2 (effect size, *d* = 0.8) which is considered to clinically indicate a change in motor function. A two-sided 5% significance level and 90% power were considered, and calculations indicated the requirement of approximately 28 participants in each group. Estimating a 30% dropout rate, each group will require 40 initial participants. Therefore, this study will be performed as a multicenter randomized controlled trial (RCT) by recruiting 80 subjects for a period of 2 years. Patients will be recruited from Pusan National University Hospital, Yangsan Pusan National University Hospital, Pusan Dongeui Hospital, and Bundang Cha Hospital.

In the event of a direct injury in relation to this study, appropriate medical action may be taken according to the decision of the clinical researcher. The level of compensation shall be an appropriate amount for the nature of the damage, its degree of consistency, and as would be generally decided by the courts in Korea and cover the entire treatment cost until the adverse event (AE) is cured. If rehabilitation therapy is required or an after-effect is noted, appropriate compensation will be provided after assessing the disorder.

### Interventions

#### Acupuncture treatment

The acupuncture treatments are described in detail below and in Table 1.

**Table 1 Tab1:** Standards for Reporting Interventions in Clinical Trials of Acupuncture (STRICTA) checklist for the study

Item	Detail
**1. Acupuncture rationale**	1a) Each patient will be treated with non-local needle acupuncture (according to the theory of channels of TKM) at distant points and press needles on stiff joints.
	1b) Acupuncture point selection will be based on Acupuncture Medicine.^9^
	1c) Acupuncture points are based on the general principles of TKM; however, the treatment will be modified over the course of the study to accommodate the individual’s changing pattern of pain, edema, or other health issues.
**2. Details of needling**	2a) The protocol will allow for up to 17 needles and eight press needles per treatment. The number of acupuncture sessions will be modified according to the judgment of the practitioners within the maximum allowance.
	2b) The acupuncture points consist of LI4 (HeGu), LI11 (QuChi), LU9 (Tai Yuan), LR3 (Taichong), ST36 (ZuSanLi), and BL60 (KunLun) on both extremities and GV20 (Bai Hui) and EX-HN-1 (Si Shen Cong) on the head. The press needle acupuncture points consist of LI5 (Yangxi) and TE4 (Yangchi) for upper limb paralysis (affected side) and BL60 (Kunlun) and KI3 (Taisi) for lower limb paralysis (affected side) in spastic palsy. In case of adverse reactions such as hematoma or pain, the treatment at that point will be skipped.
	2c) The depth of needle insertion varies with the thickness of the skin and subcutaneous fatty tissues at the acupuncture points; a depth of 1–5 mm is usually recommended.
	2d) The practitioner will determine the appropriate stimuli based on the patient’s reaction by assessing changes in palpatory findings instead of employing vigorous manipulation.
	2e) Manual stimulation will be provided via the acupuncture needles without using twisting or twirling manipulation.
	2f) Body acupuncture will be retained for up to 20 min or withdrawn immediately after the insertion of needles based on the patient’s reaction. The practitioner will provide directions for the removal of the press needle before washing hands and feet after returning home.
	2 g) The practitioner will use 0.2 mm × 1.5 mm sterilized stainless-steel needles (DONGBANG Acupuncture Inc., Korea) for body acupuncture and 0.18 mm × 1.3 mm × 1.5 mm (DONGBANG Acupuncture Inc., Korea) press needles. TKM doctors will conform to the Clean Needle Technique so as to avoid hand contamination.
**3. Treatment regimen**	3a) Group A will undergo acupuncture treatment three times a week over weeks 1–12. Group B will undergo acupuncture treatment three times a week over weeks 13–24. Each group will receive a total of 36 acupuncture treatments.
	3b) Acupuncture treatment will be administered a maximum of three times every week in 20-min sessions.
**4. Other components of treatment**	4a) For patients with spastic palsy, the practitioner will allow the patient to exercise the joint for 1 min after applying the press needle. 2. In addition to needling, thermal stimulation of the acupuncture points will be performed. 3. The patients will perform self-management activities (exercise therapy, etc.) 4. The patients will also receive herbal medicine three times per day over a period of 12 weeks parallel to the acupuncture treatment.
	4b) Patients will be informed about acupuncture in the study as follows: “In this study, a TKM doctor with more than 5 years of clinical experience will safely conduct the procedure and use pediatric disposable acupuncture needles.”
**5. Practitioner background**	5) A TKM doctor with more than 5 years of clinical experience.
**6. Control or comparator interventions**	6a) Restricting the type and frequency of rehabilitation treatments limits the potential benefits of rehabilitation therapy and is not consistent with research ethics. According to a prior observational study, children with CP in Korea undergo UR 5.74 times per week on an average [7]. Based on this, the minimum number of rehabilitation treatments is set at twice a week
	6b) The control group will continue to receive UR at least twice a week during the study period (types and number of rehabilitation treatments and rehabilitation institutions for UR are not limited).

*UR* usual rehabilitation, *TKM* traditional Korean medicine

